## Analysis

Descriptive statistics will be calculated for all variables of interest. Continuous measures will be summarized using means and standard deviations whereas categorical measures will be summarized using counts and percentages.

We hypothesize that the enhanced feedback intervention will lead to greater improvements in quality of care for patients with diabetes and/or IHD. The analysis to test this hypothesis will be carried out using multilevel hierarchical modeling (using the generalized estimating equation approach) to control for the effects of clustering as well as adjusting for multiple covariates, including the variables used in the minimization (baseline values for BP, LDL, the composite process score, and the number of patients with diabetes and/or IHD). Analysis will be performed on an intention-to-treat basis. No interim analyses are planned. Prior to analysis, other covariates will be assessed for the presence of multicollinearity; when the tolerance statistic value < 0.4 only one member of a correlated set will be retained for the model. Primary analyses will be conducted on patient level variables, combining patients with diabetes and/or IHD. Sub-group analyses will be performed on patients with only IHD, only diabetes, or both, to assess the same outcome variables.

The efficacy of the worksheet intervention will be assessed as a planned secondary analysis in two ways. First, we will test whether full completion of the worksheet resulted in improved outcomes. Full completion of the worksheet will be evaluated according to whether they declared specific and measurable goals, completed all sections of the action plan, and confirmed their commitment with their signature. Second, we will examine if physicians achieved greater improvements in the specific clinical topics that they chose to target using the worksheet.

All analyses will be carried out using the SAS Version 9.2 statistical program (SAS Institute, Cary, NC, USA).

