### Participants and data collection

Through the Electronic Medical Record Administrative data Linked Database (EMRALD), family physicians from all regions of Ontario who have been using Practice Solutions^® ^Electronic Medical Records (EMRs) for at least 12 months have signed a data-sharing agreement with the Institute for Clinical Evaluative Sciences (ICES) where EMRALD is held. ICES is a prescribed entity, under the province of Ontario's Personal Health Information Protection Act, which allows for the collection of individual level health information for use in planning and managing the healthcare system.

At ICES, mechanisms to extract, securely transfer, and de-identify the EMR data have been established[25]. For patient visits, consultations, investigations, and treatments, data in EMRALD compare well with (and often out-perform) administrative databases [unpublished data]. Furthermore, algorithms to identify patients in the EMRALD database with diabetes (sensitivity 83.1%, specificity 98.2%) [26] and IHD (sensitivity 72.4%, specificity 99.6%) [27] have been validated. Since publishing those papers, we have made further improvement to the diabetes algorithm (by considering the 'problem list' and 'past medical history' fields in addition to the lab tests and prescriptions) resulting in a sensitivity of 90.9% and specificity of 99.2%. The algorithm for identification of the IHD algorithm has also been improved by continuing to refine the search terms used to identify patients in the 'problem-list' and 'past medical history' fields. The algorithms developed for EMRALD do not require any special coding or data input by the participating physicians.

Family physicians were originally invited to participate in EMRALD through convenience sampling of EMR users. Presently, all participants work in multi-provider clinics and nearly all have access to allied healthcare providers. As a result, participants are not necessarily representative of all Ontario family physicians or of all primary care EMR users. However, this concern is partially mitigated by the varied characteristics of physicians in the sample (Table 1). As EMRALD continues to recruit new family physicians, the diversity of the sample is expected to grow. The number of participating physicians and practices in EMRALD may grow by as much as 50% during the first six months of this trial.

**Table 1 T1:** Characteristics of initial 14 clinics and 54 family physicians in the trial

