### Allocation and blinding

Given the small number of practices (clusters) involved in EMRALD, simple randomization cannot be expected to generate two similar arms for this trial. Instead, minimization was used to achieve balance at baseline across the three primary outcomes and the number of patients in each cluster who have diabetes and/or IHD. Using the baseline data for each cluster, these variables were classified as high or low using the median value as the cut-point. This was conducted with the free software, 'MINIM' [39]. Enrolment will continue for a maximum of six months; new practices will be minimized using their baseline data.

Although minimization has been criticised for increasing the risk for selection bias [40], the benefits of achieving balance at baseline through the use of minimization outweighs the minor risks involved (especially for small trials) and therefore has been widely recommended [41,42]. We believe that risk of selection bias is low in this case because the recruitment of the first fourteen practices (clusters) was completed prior to allocation of the practices using the minimization software. Furthermore, allocation of practices will remain concealed; study IDs will be used to ensure that the audit process and statistical analysis will be blinded with regard to group assignment. A research coordinator who is otherwise unaffiliated with the study will use a master list with study IDs and participant names to prepare the intervention materials. Participants will not be told explicitly which arm they are in; those in the enhanced feedback group will not be aware that the worksheet is the essential aspect of the intervention.

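### The primary GEE analysis and the sample size make no allowance for few practices (14, at most about 21), so a standard GEE test would exceed its nominal 5% level

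*Protocol article*

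**What the plan says.** The Analysis section of the protocol article names one method for the primary comparison: "multilevel hierarchical modeling (using the generalized estimating equation approach) to control for the effects of clustering as well as adjusting for multiple covariates". The adjustment set is given as "including the variables used in the minimization (baseline values for BP, LDL, the composite process score, and the number of patients" with diabetes and/or IHD), and further covariates may be added after a collinearity check. The same section says that the primary analyses use patient-level variables.

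Allocation was by practice. Allocation and blinding describes the minimization factors as practice-level: "Using the baseline data for each cluster, these variables were classified as high or low using the median value as the cut-point". It also says that "the recruitment of the first fourteen practices (clusters) was completed prior to allocation". Table 1 is captioned "Characteristics of initial 14 clinics and 54 family physicians in the trial". Growth is possible: "The number of participating physicians and practices in EMRALD may grow by as much as 50% during the first six months of this trial". That would give at most 14 × 1.5 = 21 practices.

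The article recognises that the number of clusters is small, but uses this only to justify the allocation method: "Given the small number of practices (clusters) involved in EMRALD, simple randomization cannot be expected to generate two similar arms" for the trial.

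**The concern.** The usual GEE test divides the estimate by a sandwich standard error and refers the ratio to the normal distribution. Both steps are justified by a large number of clusters. The number of patients does not help, and the Sample size section itself says that power in cluster trials comes mainly from the number of clusters. With about seven practices per arm, the sandwich standard error is biased downward and 1.96 is too small a multiplier. Each covariate that varies only between practices uses up one of about 12 between-practice degrees of freedom and makes both problems worse.

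All three primary outcomes depend on this one method. If the test does not hold its level, a worksheet with no effect is declared different from simple feedback more often than 5% of the time, and the reported intervals cover less than 95%.

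**Working it through.** **1. The plan's own sample size.** Inputs from Sample size: SD 20 mmHg, difference 7 mmHg, two-sided α 0.05, power 80%, mean cluster size 328, ICC 0.05.
- Patients before inflation: 4 × (1.96 + 0.8416)² × 20² / 7² = 256.3, which is 129 per arm or 258 in total, as stated. This is the normal approximation; an exact t-test on patients gives 260.
- VIF: 1 + 327 × 0.05 = 17.35 (stated as 17.4). 258 × 17.4 = 4,489, and 4,489 / 328 = 13.7 clusters, as stated.

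The figure reproduces. It uses patient-level critical values, and between-practice degrees of freedom do not enter.

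**2. The same design with between-practice degrees of freedom.** 14 × 328 = 4,592 patients. Divided by 17.35, this is an effective 264.7, or 132.3 per arm. SE = 20 × √(2/132.3) = 2.46 mmHg, and 7 / 2.46 = 2.85. By the non-central t distribution, power at 7 mmHg is 74% on 12 df (14 − 2) and 70% on 8 df (14 − 2 − 4). The detectable difference is about 7.5 to 7.9 mmHg for systolic BP and 0.34 to 0.35 mmol/L for LDL.

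**3. Type I error of standard GEE, by simulation.** Set-up: patient-level data with no treatment effect, exchangeable GEE with estimated correlation, sandwich SE, cut-off 1.96, and allocation by minimization on four practice-level high/low factors; 2,000 runs per cell (Monte Carlo error about 0.5 to 1 point). Practice sizes are assumed, chosen to give the Table 1 total of 4,593 and median of 263. Covariates were simulated as unrelated to the outcome, so 0.05 is the ICC left after adjustment.

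| Practices | ICC | No covariates | Baselines at patient level, practice size at practice level | All four at practice level |
|---|---|---|---|---|
| 14 | 0.05 | 9.4% | 12.7% | 18.0% |
| 14 | 0.01 | 12.0% | 13.3% | 22.1% |
| 12 | 0.05 | 11.4% | 13.4% | 24.3% |
| 21 | 0.05 | 7.6% | 8.5% | 12.9% |

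The ICC of 0.01 is the article's planning value for the composite score. The row for 12 practices is its scenario of losing two clinics. Other checks at 14 practices and ICC 0.05:
- Simple 7:7 randomization with four practice-level covariates gives 19.8%.
- Equal practice sizes, simple randomization and no covariates give 9.2%, so unequal size is not the cause.
- Model-based GEE standard errors give 9.9% to 18.5%.
- A separate simulation on practice means (20,000 runs, weights from the true ICC, no minimization) gives 9.7%, 11.3% and 20.0% with zero, one and four practice-level covariates.

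**4. Where the excess comes from.** In the 14-practice, ICC 0.05 row, the mean SE divided by the true SE is 0.910, 0.845 and 0.733. Referring 1.96 times each ratio to t on 12, 11 and 8 df gives:
- P(|t₁₂| > 1.784) = 10.0%
- P(|t₁₁| > 1.656) = 12.6%
- P(|t₈| > 1.437) = 18.9%

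These are close to the simulated 9.4%, 12.7% and 18.0%. The multiplier alone (1.96 with an unbiased SE) would give 7.4% on 12 df and 8.6% on 8 df. The rest is the SE bias.

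**5. With a correction.** Scaling the variance by K/(K − p), where K is the number of practices and p the number of practice-level parameters, and using t on K − 2 − (practice-level covariates) df gives 4.6% to 5.6% at 14 practices and ICC 0.05, and 6.6% to 7.9% at ICC 0.01. In the practice-means simulation, the Kauermann-Carroll variance with a t reference gives 5.1%, 5.2% and 6.6% with zero, one and four practice-level covariates.

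**The case against.** The strongest reply is that the article fixes the model class, covariates, intention-to-treat principle and software, but not the variance estimator, reference distribution or working correlation. Such details commonly sit in the statistical analysis plan, which is not shown and might contain a correction. This stands to the extent that a reader might infer that the trial's test will in fact run at 10–20%, and the documents do not support that. The error rates belong to standard GEE and must be stated conditionally. The reply does not dispose of the point. The article chose the inference method for the primary outcomes, that method in its standard form does not hold its level with this many practices, and the sample size leaves no room for few clusters either.

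Second, a reader might take a fourfold error rate as the expected case. That needs all four adjusters at practice level. The practice-level high/low coding is described for allocation, whereas the Analysis section speaks of baseline values and patient-level variables. Patient-level baselines are a fair reading, and then only practice size is necessarily at practice level.

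Third, 14 is the initial number of practices, not necessarily the final one. Growth to 21 would reduce the excess but not remove it, and it is not assured.

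Finally, a reader might object to calling GEE a hierarchical model. That is terminology, changes no number, and is not part of this point.

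**Conclusion.** The concern holds in conditional form. The article applies GEE to an initial 14 practices (at most about 21), adjusts for the minimization variables, and allows for few clusters in neither the analysis nor the sample size. Run as standard GEE at an ICC of 0.05, the nominal 5% test has a type I error of about:
- 10–13% at 14 practices with at most one practice-level covariate;
- up to 20% at 14 practices with all four at practice level;
- 7–13% at 21 practices across these covariate choices.

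The composite score's ICC of 0.01 gives slightly higher figures. No uncorrected scenario examined returned to 5%. The result rests on an uncorrected Wald test and on assumed practice sizes matched to Table 1. The covariate level and the final number of practices, which the article leaves open, decide where in the range the trial would fall.

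**What to change.** In the Analysis section, state that inference uses exchangeable GEE clustered on practice, with a small-sample-corrected variance (for example Kauermann-Carroll or Fay-Graubard) and a t reference with df = practices − 2 − number of practice-level covariates. A linear mixed model with a random practice effect and Kenward-Roger degrees of freedom is equally acceptable. State also that baseline BP, LDL and process score enter as patient-level values where available, so that practice size is the only minimization variable that must use a practice-level degree of freedom. A permutation test that respects the minimization is optional.

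The design does not change. The cost is a sentence or two, a little programming and wider intervals. At 14 practices and ICC 0.05, the average widening over the uncorrected interval would be about 2.179 / (1.96 × 0.910) = 1.22 times with no covariates and 2.201 / (1.96 × 0.845) = 1.33 times with one practice-level covariate. With four it would be 2.306 / (1.96 × 0.733) = 1.61 times, which is the reason to keep practice-level terms few. The power statement should be reworked on the same degrees of freedom.

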### Analysis

#### Outcomes

There will be two disease primary outcomes and one process primary outcome. The disease primary outcomes will be the patients' most recent LDL and systolic BP values, if they have been tested within 24 or 12 months, respectively. Though these are actually risk factors, they are the target of cardiovascular risk management, and are therefore appropriate given the brevity of the trial.

The process primary outcome is a composite process score indicating whether patients with diabetes and/or IHD are receiving the recommended prescriptions and tests within the appropriate timeframes. These evidence-based quality indicators are concordant with guidelines [43-48] and are comparable to composite scores used in similar studies [47]. All patients with diabetes and/or IHD will receive a composite process score with a maximum of 6. For patients with diabetes, a maximum score of 6 would indicate testing of urinary microalbumin and serum LDL within a year, measuring BP and glycosylated haemoglobin within six months, and having active prescriptions for a statin and an angiotensin-modifying agent. For patients with IHD, a maximum score of 6 would indicate testing fasting blood glucose within two years and LDL within one year, measuring BP within six months, and having active prescriptions for aspirin, a statin, and an angiotensin-modifying agent. For patients with both diabetes and IHD, the maximum raw score will be 7 (based on the same indicators as diabetes but adding aspirin), but this will then be multiplied by 6/7 to standardize to a maximum score of 6, as outlined in Table 2.

**Table 2 T2:** Composite process score to be calculated for each patient as primary process outcome; the score is calculated differently for patients with diabetes, ischemic heart disease, or both.

Quality indicator (for each patient receives a score)	Diabetes (max score = 6)	IHD (max score = 6)	Both Diabetes + IHD (multiply by 6/7 for max score = 6)
BP test in 6M	X	X	X

A1C test in 6M	X		X

FBG test in 24M		X	

LDL test in 12M	X	X	X

ACR test in 12M	X		X

Rx ASA		X	X

Rx Statin	X	X	X

Rx ACE/ARB	X	X	X

IHD = ischemic heart disease, BP = blood pressure, A1C = glycolated haemoglobin, FBG = fasting blood glucose, LDL = low density lipoprotein cholesterol, ACR = urinary albumin-to-creatinine ratio, ASA = aspirin, ACE/ARB = angiotensin-modifying agent

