Secondary outcomes were chosen because they may be the targets of action by recipients of the intervention. Thus, the secondary outcomes include: the proportion of patients whose results meet the targets recommended in guidelines for glucose, LDL, and BP; and the prescriptions rates for insulin, beta blockers, angiotensin-modifying agents, aspirin, and statins.

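### The named adjustment covariates give each primary outcome its own baseline but not the glucose-target and prescribing outcomes; adding those terms is a cheap precision gain (minor, secondary outcomes only)

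*Protocol article*

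**What the plan says.** The Analysis section states the hypothesis in terms of change: "We hypothesize that the enhanced feedback intervention will lead to greater improvements in quality of care". The model is a GEE that adjusts for several covariates, among them those of the allocation scheme, which are listed as "baseline values for BP, LDL, the composite process score, and the number of patients with diabetes and/or IHD". Further covariates are foreseen without being named, and they pass through a screen: "other covariates will be assessed for the presence of multicollinearity; when the tolerance statistic value < 0.4 only one member of a correlated set will" (the sentence ends by saying that this one member stays in the model).

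The Outcomes section lists as secondary outcomes "the proportion of patients whose results meet the targets recommended in guidelines for glucose, LDL, and BP", together with "the prescriptions rates for insulin, beta blockers, angiotensin-modifying agents, aspirin, and statins". Three of these drug classes are also items of the composite score. For IHD patients, for example, a full score requires "having active prescriptions for aspirin, a statin, and an angiotensin-modifying agent" in addition to the tests. Table 2 scores aspirin only for patients with IHD, alone or with diabetes.

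Under Allocation and blinding, "minimization was used to achieve balance at baseline across the three primary outcomes"; the fourth factor was how many eligible patients each practice had. No secondary outcome was a minimization factor.

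**The concern.** The named covariates follow the allocation scheme and not the outcome being analysed. Set against the outcomes, they cover:

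- **BP, LDL and composite (primary):** each has its own baseline.
- **BP and LDL targets:** the baseline value of the same measurement is named.
- **Statin, ACE/ARB and aspirin rates:** each is one item in a sum of six or seven, and aspirin is not scored for patients with diabetes alone. The baseline composite is a diluted proxy.
- **Glucose target, insulin and beta-blocker rates:** no related term. Table 2 counts whether A1C or fasting glucose was tested, not the result, and neither drug class is in the composite.

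A patient's or practice's starting level may be the best available predictor of the later level for prescribing and glycaemic control. With few practices and no balancing on these rates, the arms can start some points apart by chance. A model without the starting level then estimates the arm difference with more noise than the data require. The Outcomes section says these outcomes were chosen because physicians may act on them, so it is worth estimating them well.

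**Working it through.** **The plan's own figure.** The Sample size section gives SD 20 mmHg, difference 7 mmHg, two-sided α 0.05, power 80%, mean cluster size 328 and ICC 0.05.

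- Per arm: 2 × (1.960 + 0.842)² × 20² / 7² = 128.1, rounded up to 129, so 258 in total, as stated.
- VIF = 1 + 327 × 0.05 = 17.35 (stated as 17.4). 258 × 17.4 = 4,489, and 4,489 / 328 = 13.7 clusters, as stated.

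No corresponding figure is given for any secondary outcome, so what follows is illustration.

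**Chance baseline gap in a rate that was not minimized.** Assumptions: 14 practices split 7 and 7, 328 patients each (2,296 per arm), rates of 15% and 40%. SD of the gap = √[2p(1 − p) × VIF / 2,296]. Three ICCs are used: 0.05 (the value presumed for BP), 0.01 (the rounded value for the composite) and 0.0059 (the pilot value for the composite). The VIFs are 17.35, 4.27 and 2.93.

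| Rate | ICC 0.0059 | ICC 0.01 | ICC 0.05 |
|---|---|---|---|
| 15% | 1.8 points | 2.2 points | 4.4 points |
| 40% | 2.5 points | 3.0 points | 6.0 points |

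For example, at 40% and ICC 0.05: √(2 × 0.24 × 17.35 / 2,296) = √0.003627 = 0.060.

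For scale, the Background reports a median gain of 5% for feedback on dichotomous outcomes in the systematic review that it cites. A gap above 5 points at a 40% rate has probability of about 41% at ICC 0.05, 9% at ICC 0.01 and 4% at ICC 0.0059 (normal approximation).

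**Gain from the own-baseline term.** Let r be the correlation between baseline and final value that remains after the named covariates. The SE is multiplied by √(1 − r²):

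- r = 0.3: 0.95
- r = 0.5: 0.87
- r = 0.7: 0.71
- r = 0.9: 0.44

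**Detectable difference with 80% power** (2.80 × SE), at a 40% rate, taking the SE without the own-baseline term as the SD of the gap above:

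| ICC | No own baseline | r = 0.3 | r = 0.5 | r = 0.7 | r = 0.9 |
|---|---|---|---|---|---|
| 0.05 | 16.9 | 16.1 | 14.6 | 12.0 | 7.4 |
| 0.0059 | 6.9 | 6.6 | 6.0 | 5.0 | 3.0 |

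The columns with r are gains over the named covariate set only if r is what remains after that set. For statin, ACE/ARB and aspirin the baseline composite already takes up part of the correlation, so a lower r applies. The figures use a normal approximation on the risk-difference scale and ignore the small number of clusters.

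**The case against.** The strongest reply is that the list is open. The covariates are introduced by the word including, and unnamed others are foreseen. The text neither says that one fixed set serves every outcome nor excludes own-baseline terms. The plan to look at improvement in the topics that physicians chose also suggests that starting values will be used somewhere. This stands. A reader might infer that the protocol has fixed a model that compares 24-month rates without the starting rate; the document does not say so. What remains is that nothing secures these terms. Any that are added as other covariates fall under a screen that drops one of a correlated set without saying which.

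The second reply is that covariate lists for each secondary outcome belong in the analysis plan, which is not shown. This also has weight and is a reason for the low priority. The point is not the silence: the article does name baseline covariates, and the named set suits the primary outcomes better than these.

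The third reply concerns bias. A reader might infer that a chance difference in starting rates makes the comparison biased or raises the false-positive rate. Nothing in the document supports that. Under fair allocation the standard error already reflects chance imbalance. The loss is in precision, and in an estimate that is not corrected for the imbalance that actually occurred.

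Finally, a reader might infer that omitting own baseline doubles the standard error. That needs r near 0.9 after the other covariates, and the large absolute figures also need the BP ICC of 0.05. The only ICC estimated from pilot data for a process measure is 0.0059, which gives an SE near 2.5 points and a detectable difference near 7 points at a 40% rate.

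**Conclusion.** The point holds as a minor one, for secondary outcomes only. The named covariates contain no own-baseline term for the glucose target or for any individual prescribing rate. The gap is clearest for the glucose target, insulin and beta blockers and only partial for statin, ACE/ARB and aspirin. The consequence is avoidable imprecision and unadjusted chance imbalance, not systematic bias, and it arises only if the open list is not completed with these terms.

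The gain could be anything from about 5% off the standard error (r = 0.3) to more than half (r = 0.9). The document gives no rate, ICC or baseline correlation for these outcomes, so it cannot be narrowed further. The primary outcomes are not affected.

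**What to change.** Add to the Analysis section that each secondary outcome model also includes that outcome's own baseline value, measured on the patient: prescription status for the drug class concerned, or target status for glucose, from the baseline EMR upload. State two further things: that this term is kept regardless of the collinearity screen, and one prespecified way of handling patients who have no baseline record.

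The cost is a few lines of text and one more covariate per model, from data that the baseline upload should already hold. No new data or patients are needed. The small downside is that the covariate set then differs by outcome. Settling it before the 24-month analysis also avoids choosing covariates after the results are seen.
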